#### Play Behaviour

A base map of the outdoor space (a geographical mapped representation) used by each ELC setting will be developed for recording children’s play behaviours using Google Maps. A base map allows observers to document the physical features and layout of the outdoor environment such as vegetation, play structures, and pathways [23]. The Tool for Observing Play Outdoors (TOPO) will be used to code pre-determined play types onto the base map of the outdoor space [19]. This study will use a place-based protocol to assess the quality of the environment for supporting play types [23]. A pre-defined observation zone will be scanned clockwise until a play event is detected. The researcher then observes the child(ren) for around 15 s, records the play behaviours, and maps the event onto the base map. Afterwards, scanning of the observation zone begins again from the point that it stopped, until another play event is detected. Only data from children who have consent from their parent/carer to participate will be recorded. The expanded TOPO-32 version will be used to assess the feasibility of fully completing the data collection tool. The tool has 9 primary play types: physical play, exploratory play, imaginative play, play with rules, bio play (interactions with the natural environment), expressive play, restorative play, digital play, and non play, along with 32 associated subtypes. The TOPO-32 assigns primary-subtype combinations for each observed play episode alongside peer, adult, and environmental interaction codes. For each play episode, two primary-subtype combinations will be recorded. Additional categories will be added to the observation tool such as risk taking during play. Our observation protocol will use the play categories defined by Sandseter and colleagues (Table 6) as these are considered the most suitable approach for identifying the risk-taking affordances [24,25,26]. Appendix B has an example of the observation protocol to be used in the study.

#### Semi-Structured Interviews

Using a semi-structured interview guide (Appendix A), developed using the Normalisation Process Theory, acceptability of the programme and study design methods will be assessed with ELC headteachers and practitioners. Interviews will cover participants’ views on the implementation of nature-based ELC (e.g., staff support, access to training and resources, contextual factors that influence implementation such as weather) and acceptability of the study design methods (how easy/difficult ensuring children remain in assigned groups, are data collection methods too intrusive, did the presence of an external researcher impact delivery of the programme in any way). Interviews will last one hour and take place in person or over the phone, whichever is most convenient to the participant. Interviews will be audio recorded and transcribed verbatim.

#### Monitoring and Evaluation Tools

Our EA workshops identified several data collection methods that are already in place within ELC settings to record children’s progress throughout their time at the settings. These are known as online journals. A sample of these data collection methods will be requested from participating children. The online journals will be examined to check for similarities of the type of information recorded and to determine whether standardised analysis may be implemented across the online journals from each ELC setting. A sub-sample of 5 participants from each participating ELC setting will be selected at random. OT will ask the headteacher/manager for access to the information collected within the online journals of children who have consent from their parents. An Excel spreadsheet will be developed based on the information extracted from the online journals. This information will include what outcomes are recorded, how many times, and by whom.

## 2.9. Analysis

### 2.9.1. Data Management

All data will be stored in a secure storage system at the Social and Public Health Sciences Unit (SPHSU), University of Glasgow. The raw data will only be accessible to the immediate research team. Consent forms will be stored separately from participant data and a unique identification code will be assigned to each participant and ELC setting. Raw data such as interview recordings and identifiable transcripts will be securely deleted at the end of the project timeline. The de-identified data will be stored for up to 10 years and be available to researchers who are interested and have relevant ethical approval in an anonymised format in line with the University of Glasgow retention policy and general data protection regulation.

### 2.9.2. Recruitment

The feasibility of the recruitment methods and retention rates will be determined by calculating the proportion of children measured at baseline and follow-up. Participant characteristics of those who complete the study and those who drop out will be investigated to determine any sources of bias. 

### 2.9.3. Statistical Analysis

Baseline characteristics of the children and ELC settings will be summarised descriptively using means and standard deviations. For outcome measures: medians and interquartile ranges will be calculated for continuous variables and frequencies and percentages for categorical variables. The summary statistics will be examined alongside demographic variables to inform the sample size and recruitment methods for the full-scale evaluation. Comparisons will be made by the SIMD level of ELC settings. Any missing data will be described to inform the full-scale evaluation. STATA statistical software will be used for all analyses.

Exploratory inferential analysis using ANOVA and linear regression will be performed within the study population of each ELC setting. Analysis will include a covariate adjustment based on the confounding variables collected in the demographic survey (e.g., gender, SIMD score, ethnicity, etc.) and covariate adjustment using children’s physical activity levels, since higher levels of PA are known to positively influence mental wellbeing.

Using propensity score matching, we will estimate the average treatment effect (ATE) of attendance at nature-based ELC on each health and wellbeing outcome (e.g., PA). A logistic model will predict each participant’s propensity score using the covariates collected in the demographic survey. The ATE on an outcome will be estimated by matching participants to another participant whose propensity score is within the pre-specified caliper distance.

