## 1. Introduction

The early learning and childcare (ELC) environment is an important setting to support healthy child development. Providing outdoor nature-based play and learning in the early years (0 to 5 years) setting can encourage children to be physically active and develop their social and cognitive skills, while helping them maintain a healthy weight later in life and support more equitable access to local green spaces [1]. However, there is a growing concern that the increasing availability of tablets, smart phones, and television watching, along with a high number of risk averse parents, is culminating in children who are less physically active, who are spending a lot of time indoors, and who have interrupted sleep patterns [2,3,4]. By providing children with more time outdoors in rich green spaces, nature-based ELC could be a key approach for supporting children’s physical, social, and emotional development.

The UK Chief Medical Officers recommend that preschool-aged children (3–4 years) should spend at least 3 h per day physically active, including 1 h in moderate-to-vigorous physical activity (MVPA) [5]. However, research suggests that preschool-aged children struggle to meet the recommendations for MVPA and spend most of their time in low physical activity (PA) [6,7]. MVPA is associated with positive mental health, cardiorespiratory fitness, and body mass index (BMI) in adolescence, therefore it is important to promote these healthy behaviours in the early years [8,9]. Being outdoors is a positive correlate for PA in children [10]. Furthermore, PA, especially outdoor play, is positively associated with most sleep outcomes in preschool-aged children [11]. The natural outdoor environment has a variety of affordances that have the potential to support children’s development of their motor competence, social skills, mental wellbeing, and physical health [10,12,13,14]. A recent review of the literature found positive associations for sedentary time and balance (a key component of motor competence) among children attending nature-based ELC [15]. However, the authors concluded that more high-quality research is required that better describes the nature exposure and outcome measurement tools [15].

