2. To what extent can ***propensity score matching*** based on multiple treatment groups be suitably applied within this context?	Data collected on number of children successfully matched across all participating ELC settings.	Children’s demographic information used for matching.	Observed covariates are recorded in both groups. A propensity score is calculated based on these characteristics. Propensity score of children in fully outdoor settings and satellite settings will be matched with propensity score of children in traditional ELC settings. The difference in average outcomes of the matched pairs are compared and a local average treatment effect is estimated. To reduce the risk of bias, matching will be combined with difference-in-differences method, facilitates correction of differences between groups that are fixed over time (reduces the risk of bias in the estimation).	Participating children in all participating ELC settings in Glasgow.	Average treatment effect will be calculated based on the propensity scoring matching of participants from each group.
3. What ***outcomes*** should be included in a future impact evaluation and how should they be measured?	Data collected on outcome measurements using, device worn measurements, questionnaires, and observations. Completeness of data collected and ease of use regarding measurement tools. Which outcome measurement tools identify a change in effect from baseline to follow-up (positive, negative, or null)?	Weight and height: portable standiometer and digital scales. Motor competence: Preschool Gross Motor Quality Scale (PGMQS)PA and sleep: Axivity device. Social and emotional outcomes: strength and Difficulties Questionnaire (SDQ). Play: Tool for Observing Play Outdoors (TOPO). Semi-structured interviews.	Baseline: weight and height, PGMQS, Axivity (7 days with a minimum of 3 full consecutive days), SDQ. TOPO will be implemented during exposure period. Follow-up: weight & height, PGMQS, SDQ, Axivity. Semi-structured interviews with managers and practitioners. Parents will be given a questionnaire at the end of the study asking how the SDQ and Axivity measurement tools were received.	Participating ELC settings in Glasgow, children, staff, and parents/carers.	Summary statistics will be presented for the outcome measures, means and standard deviations will be presented.

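### The exploratory regression adjusts for physical activity, a study outcome and likely mediator, so any comparison of provision models from it would be net of physical activity

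*Protocol article*

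**What the plan says.** Section 2.9.3 describes an exploratory ANOVA and linear regression, to be run within each setting's study population. The adjustment set is the demographic confounders plus children's PA, "since higher levels of PA are known to positively influence mental wellbeing". The clause does not say which PA measurement is meant, nor which outcomes it covers.

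The next paragraph of the same section treats PA as a result of exposure: propensity score matching is to estimate the "average treatment effect (ATE) of attendance at nature-based ELC on each health and wellbeing outcome (e.g., PA" is the example given). Table 1, in the row for research question 3, lists the activity monitor among the repeated outcome measures: "Follow-up: weight & height, PGMQS, SDQ, Axivity". Table 4 shows it at weeks 0 and 5.

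The introduction supplies both links of a causal chain. From exposure to PA: "Being outdoors is a positive correlate for PA in children". From PA to wellbeing: "MVPA is associated with positive mental health, cardiorespiratory fitness, and body mass index (BMI) in adolescence". It also associates PA, outdoor play above all, with most sleep outcomes in preschool children. A later paragraph says that natural features prompt children to be active and explore, to the benefit of their social skills and wellbeing.

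**The concern.** A covariate belongs in a model for the effect of provision if it is a common cause of provision and outcome, or if it predicts the outcome and is not itself changed by provision. The reason given in section 2.9.3 establishes only that PA predicts wellbeing. Set beside the introduction, it describes a variable lying between outdoor provision and wellbeing. Holding such a variable fixed removes the part of the effect that runs through it. It can also introduce confounding by unmeasured common causes of PA and the outcome.

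This matters even in a feasibility study. Section 2.8.2 says that estimated programme effects will help decide which outcomes become primary and secondary in the powered evaluation. Section 2.8.1 favours measures that show a signal, and Table 3 makes a between-group difference part of the green criterion for research question 3. If PA-adjusted estimates inform that judgement, the outcomes that work through PA are the ones most likely to look null.

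**Working it through.** The plan gives no effect size, standard deviation or powered comparison, so there is no stated figure to reproduce. The check has three parts.

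**1. Where PA enters.** PA is a covariate only in the exploratory ANOVA and regression. The propensity model uses the demographic survey (sections 2.7 and 2.9.3), and the items listed for that questionnaire in section 2.8.2 do not include PA. Table 1 adds difference-in-differences to the matching, again without PA as a covariate.

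**2. Whether the regression contains a provision contrast.** Each setting delivers one model (sections 2.2 and 2.6). Inside one setting the provision indicator is constant and duplicates the intercept. A design with intercept, provision and PA then has rank 2 of 3, and no provision effect can be estimated. The loss below therefore applies to an exploratory regression that pools settings and compares models.

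**3. Size of the loss in a pooled linear model.** Let a be the effect of provision on PA (in SD), b the effect of PA on the outcome (per SD of PA), and c the direct effect of provision.

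- Total effect = c + a × b
- PA-adjusted coefficient = c (no unmeasured common causes of PA and outcome)
- Share removed = a × b / (c + a × b)

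All values of a, b and c are assumptions; none comes from the protocol.

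| a | b | c | Total | PA-adjusted | Removed |
|---|---|---|---|---|---|
| 0.2 | 0.1 | 0.2 | 0.22 | 0.20 | 9% |
| 0.2 | 0.1 | 0.1 | 0.12 | 0.10 | 17% |
| 0.5 | 0.1 | 0.2 | 0.25 | 0.20 | 20% |
| 0.2 | 0.3 | 0.2 | 0.26 | 0.20 | 23% |
| 0.5 | 0.1 | 0.1 | 0.15 | 0.10 | 33% |
| 0.2 | 0.3 | 0.1 | 0.16 | 0.10 | 38% |
| 0.5 | 0.3 | 0.2 | 0.35 | 0.20 | 43% |
| 0.5 | 0.3 | 0.1 | 0.25 | 0.10 | 60% |
| 0.2 or 0.5 | 0.1 or 0.3 | 0 | 0.02 to 0.15 | 0 | 100% |

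Least-squares fits to simulated data, 400,000 records per scenario, agreed with these formulas to within 0.01.

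**The case against.** The strongest reply is about scope, and most of it stands.

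- A reader might infer that the study's main estimate of the effect of attendance is distorted. It is not: that estimate is the propensity-matched one, which does not use PA.
- Read literally, the within-setting regression compares no provision models, so nothing is lost from a contrast that is not there. That is correct, but the wording then leaves unclear what the model is for. The demographic confounder adjustment suggests a comparison, and the passage needs reconciling.
- No progression decision names the PA-adjusted model. Table 1 assigns summary statistics to research question 3. The route into outcome selection is therefore possible, not fixed.
- The time point of PA is unstated, and PA measured before exposure would be a legitimate covariate. However, section 2.5 enrols children who already attend, and Table 2 caps prior outdoor exposure for satellite children only. For fully outdoor children, baseline PA is recorded after exposure has begun.
- One could read the clause as adjusting PA for PA. The reason given concerns mental wellbeing only, so that is probably not intended, although the text does not exclude it.
- Bias toward no effect is not certain. It requires direct and indirect effects of the same sign, and confounding of PA with the outcome could push either way. The introduction reports correlates and associations, the mental health one in adolescents. For balance the chain is weaker still: the motor-skill subsection of 2.8.2 presents motor skills as influencing PA, not the reverse.

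What remains is that the stated reason does not justify the adjustment in any model meant to show the total effect of provision.

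**Conclusion.** The point holds for the exploratory regression only. On the protocol's own account PA is an outcome of attendance and a likely mediator for wellbeing and sleep. An exploratory comparison of provision models that adjusts for it would not estimate the total effect of provision. Under the assumed linear model, with direct and indirect effects of the same sign, the loss runs from about 9% to 100%, reaching 100% only when the whole effect passes through PA. No single figure in that range can be called the plan's loss. Severity is moderate: the model is labelled exploratory, and the matched estimate is untouched.

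**What to change.** In section 2.9.3:

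1. Remove PA from the covariates of any exploratory model that estimates the effect of provision, and keep PA as an outcome.
2. If the link between PA and wellbeing is of interest, report the PA-adjusted model separately, labelled as an exploratory mediation or association analysis, and name the PA time point used.
3. Reconcile the within-setting wording with the purpose of the regression: say whether settings are pooled and which contrast is estimated.
4. If baseline values are used as covariates, whether of PA or of the outcome itself, state that for fully outdoor children they are recorded after exposure has begun. Adjusting for the baseline outcome does not escape this problem.

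The cost is a few clauses of text, with no change to data collection or sample. It should be settled before the analysis, since the model may carry over into the full evaluation.

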### 2.2. Study Design

#### Feasibility and Pilot Study

The development of this feasibility study is based on guidance from the UK Medical Research Council for developing and evaluating complex interventions [37]. This study will pilot a quasi-experimental study design method:

A quasi-experimental non-equivalent control design using propensity score matching with multiple treatment groups. Children who attend two traditional ELC settings will be assigned to the control group and matched with children from two treatment groups: (1) 2 fully outdoors ELC settings and (2) 2 satellite ELC settings. The researchers will follow guidance on implementing propensity score methods with multiple treatment groups (e.g., 2 exposure groups and a control group) [38]. From baseline to follow-up, the study duration will be 5 weeks. Play and learning will continue as normal in both settings and the outcomes mentioned below will be measured to assess the possible impact of outdoor play and learning.

This study will employ a mixed-methods approach. Both quantitative and qualitative data will be collected to address the research questions. Alongside the piloting of these two study designs, we will carry out a process evaluation using semi-structured interviews. Qualitative methods are considered an important methodological approach to understanding the causal mechanisms of complex health interventions [39].

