### 2.6. Sample Size

As this is a feasibility/pilot study, no sample size to detect between group differences was calculated. The study may provide preliminary data for the calculation of a sample size for a future full-scale evaluation. We aim to recruit 2 fully outdoor ELC settings, 2 satellite ELC settings, and 2 traditional ELC settings.

A minimum of 10 children per ELC setting will be recruited. Two practitioners and one headteacher/manager will be recruited from each ELC setting.

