The propensity score is the probability of being exposed given the values of measured confounding variables [42]. In the same manner that randomisation will on average lead to measured and unmeasured covariates being balanced between study groups, assigning participants based on their propensity score will on average lead to measured baseline covariates being balanced between the study groups [43]. Our propensity score model will include all measured baseline covariates collected in the demographic survey. Participants from the traditional ELC settings (comparison) will be matched with participants from the fully outdoor settings and satellite settings (exposure) with similar propensity scores. We will use nearest neighbour matching within a specified caliper distance that is proportional to the standard deviation of the recorded covariates [43]. Once matched, the treatment effect will be determined by directly comparing the outcome data between matched samples of the exposure and comparison groups. Researchers have shown that the use of propensity score matching with small study samples can demonstrate unbiased estimations of treatment effect if the appropriate confounding variables are included in the propensity score model [44].

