2. To what extent can propensity score matching based on multiple treatment groups be suitably applied within this context?	GREEN: 80% or more enrolled children suitably matched based on propensity scores. AMBER: 50–79% enrolled children matched. RED: less than 50% enrolled children matched.	GREEN: Strong indication that matching children based on their propensity score is a reliable comparison method to be used in a powered effectiveness evaluation. AMBER: Indication that the matching method might work in an effectiveness evaluation; however, it should be considered alongside other criteria such as the level of missing data. RED: The study design method needs careful consideration before being used again.	Determine the suitability of the covariates collected in the demographic survey are sufficient to calculate reliable propensity scores for matching.	We consider 80% to be achievable if the criteria regarding retention in RQ1 is successful.
3. What ***outcomes*** should be included in a future impact evaluation and how should they be measured?	GREEN: 70% or more measures are returned fully completed at baseline and follow-up. Outcome measures are able to identify a change from baseline to follow-up and a difference in effect between intervention and comparison groups (positive or negative). No major acceptability issues during educator interviews or via parent feedback. AMBER: Outcome measure completion rate of 60% or more. An indication that there may be a difference in effect but insufficient data to determine definitively. Three or four major acceptability issues raised by interviewees or through parent feedback; however, mitigating strategy identified. RED: Less than 60% of outcome measures completed. Major acceptability issues raised regarding measurement methods with no possible mitigation strategy.	GREEN: Strong indication to proceed with the outcome measurement methods. AMBER: Medium indication to proceed. Recommend discussing the measurement methods with research steering group. RED: Indication of doubt as to whether to proceed. Measurement methods should be discussed with steering group, taking into consideration findings from RQ6 and whether different measurement tools might be better suited to detect an effect in outcomes.	Baseline and follow-up outcome measures. Feedback from parents in activity diary. Process evaluation interviews with ELC educators.	We consider 70% completion rate sufficient to carry out analysis.

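### Each model is represented by only two settings, but the model effect is a comparison of matched children with no allowance for setting, and the RQ3 GREEN criterion leans on that difference

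*Protocol article*

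**What the plan says.** **Exposure.** Study Design (2.2) defines the groups by the setting attended: "Children who attend two traditional ELC settings will be assigned to the control group and matched with children from two treatment groups", these being two fully outdoor and two satellite settings. Section 2.6 gives the numbers: "We aim to recruit 2 fully outdoor ELC settings, 2 satellite ELC settings, and 2 traditional ELC settings", and "A minimum of 10 children per ELC setting will be recruited".

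**Estimation.** The effect is described between children. Section 2.7, under Propensity Score Matching, says: "Once matched, the treatment effect will be determined by directly comparing the outcome data between matched samples of the exposure and comparison groups". Section 2.9.3 says: "The ATE on an outcome will be estimated by matching participants to another participant whose propensity score is within the pre-specified caliper distance". Table 1 (RQ2) compares average outcomes of matched pairs and adds a difference-in-differences step. The score itself rests on the parents' questionnaire: "Our propensity score model will include all measured baseline covariates collected in the demographic survey". The ANOVA and regressions in 2.9.3 are run inside each setting, where the model does not vary, so the matched estimate is the only inferential comparison between models that the article describes.

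**Use of the result.** In Table 3, RQ3 is GREEN if, besides completeness and acceptability, "Outcome measures are able to identify a change from baseline to follow-up and a difference in effect between intervention and comparison groups". AMBER covers a possible difference that the data are too thin to settle. Section 2.8.1 considers outcomes showing a signal for progression if the other criteria are met, and 2.8.2 uses estimated effects to help choose primary and secondary outcomes for the full evaluation.

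The article mentions no clustering, ICC, setting effect or setting-level comparison of models.

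**The concern.** All children in a setting share its staff, outdoor space and routine. Section 2.4 itself says that settings differ in area, type of green space and size, and that context, dose and practice shape daily operations. With two settings per model, the model contrast is two nurseries against two other nurseries, whatever the number of children measured. The propensity score holds child and family characteristics, so matching on it cannot balance what belongs to the setting.

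The decision at stake is which outcomes go into the powered evaluation. Telling GREEN from AMBER on the difference criterion, or an effect from a null result, needs some judgement of uncertainty. If that judgement is made child to child, a chance divergence between two pairs of nurseries can pass as an effect of the model and favour one outcome measure over another.

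**Working it through.** The article gives no interval, test, ICC or powered sample size for this contrast, so there is no figure to reproduce. The check asks how much precision a child-level comparison would claim and how much the design supports.

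**Inputs**
- Settings per model: 2 (section 2.6).
- Children per setting, m: at least 10 (section 2.6), so at least 20 per model and 6 × 10 = 60 in all.
- Sensitivity: m = 8, the Table 3 GREEN retention boundary of 80%.
- ICC of the analysed outcome, ρ: not given. **Assumed** 0.01, 0.05 or 0.10. Because of the difference-in-differences step, it is the ICC of the five-week change that matters.

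**Step 1: variance of the difference between two models.** With the total variance of the change set to 1:

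- Child-level, children taken as independent: 2/20 = 0.100, SE = 0.316.
- With setting variation: 2 × [ρ/2 + (1 − ρ)/20] = ρ + (1 − ρ)/10 = 0.1 × (1 + 9ρ).

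The term ρ does not shrink when more children are measured in the same settings. The ratio of the two variances is the design effect, DE = 1 + (m − 1)ρ.

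**Step 2: consequences.** SE inflation is √DE, the effective number per model is 20/DE, and the true size of a nominal 5% child-level test is about 2 × [1 − Φ(1.96/√DE)].

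| ρ (assumed) | DE, m = 10 | SE inflation | Effective n of 20 | Type I error, m = 10 | Type I error, m = 8 |
|---|---|---|---|---|---|
| 0.01 | 1.09 | 1.04 | 18.3 | 6.0% | 5.8% |
| 0.05 | 1.45 | 1.20 | 13.8 | 10.4% | 9.2% |
| 0.10 | 1.90 | 1.38 | 10.5 | 15.5% | 13.3% |

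**Step 3: simulation.** In 40,000 null datasets per case (two models, two settings each, m = 10), a child-level t-test rejected in 6.0%, 10.4% and 16.1% of runs unpaired, and in 6.0%, 10.1% and 15.4% with children randomly paired across models. With ρ = 0 both held 5%. A t-test on the four setting means, with 2 degrees of freedom, stayed at about 5% throughout. The simulation used one normal outcome per child, to be read as the change score, and did not fit a propensity score.

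**Step 4: 95% half-widths in SD units.**
- Child level, 38 df: 2.02 × 0.316 = 0.64.
- Setting level, 2 df: 4.30 × 0.316 × √DE = 1.42, 1.64 and 1.88 at ρ = 0.01, 0.05 and 0.10.

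Even at ρ = 0.01 the setting-level interval is more than twice as wide, mainly because four settings leave only 2 degrees of freedom.

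**The case against.** The strongest reply is that the article plans no interval, p-value or significance threshold for the matched estimate. Table 1 lists summary statistics for RQ3, and section 2.6 says "As this is a feasibility/pilot study, no sample size to detect between group differences was calculated". The sentences on matching explain how pairs are formed, and the variance method could sit in a fuller plan. This stands. A reader might infer that the plan contains intervals that are too narrow, or runs a test with a 10% or 16% error rate. The document does not support either reading, because that test is supplied here for illustration.

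Difference-in-differences also does real work. Stable differences between settings cancel, and the ICC of a five-week change may be smaller than that of a single measurement. At 0.01 the inflation of the error rate is slight. What it cannot cancel is a change specific to one setting during those weeks.

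A reader might further infer that outcomes would be dropped for want of a difference. Table 3 does not say so: RED for RQ3 covers low completion and acceptability problems that cannot be mitigated, AMBER goes to the steering group, and a signal is weighed with the other criteria.

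Finally, clustering does not in itself bias the estimated difference. What would be overstated is its precision.

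None of this answers the core point. The child-to-child contrast and the GREEN criterion are both fixed in the article, so this is more than detail left to an analysis plan.

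**Conclusion.** The concern holds in this form: the only described between-model analysis compares matched children, exposure is fixed by setting with two settings per model, and RQ3 GREEN and the choice of outcomes lean on the resulting difference. Setting-specific changes over five weeks cannot be separated from the model effect by matching on child and family covariates.

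The size depends on an ICC that the document does not give. At assumed values of 0.01 to 0.10 and 10 children per setting, child-level standard errors would be too small by a factor of 1.04 to 1.38. A nominal 5% child-level test would have a true size of about 6% to 16%, slightly less with 8 children. These figures assume equal setting sizes, normal outcomes and 20 analysed children per model. They apply only if child-level uncertainty is attached to the estimate.

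The feasibility aims on recruitment, retention, completeness and acceptability are not affected, nor are the within-setting regressions.

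**What to change.** **Section 2.9.3.** State that the setting is the unit of exposure and of inference for every between-model contrast. Report matched differences together with setting-level means or plots, and give either setting-level uncertainty or no child-level p-values and confidence intervals. Report the between-setting variation (ICC) for each outcome, noting that six settings estimate it very imprecisely.

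**Table 3, RQ3.** Remove detection of a between-model difference as a GREEN condition, or mark it as descriptive only, so that the colour rests on completeness, ability to register change, and acceptability. Align sections 2.8.1 and 2.8.2 with this, so that a signal from two settings per model does not decide which outcomes go forward.

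**Cost.** Wording only, with no extra data. The stated uncertainty becomes much wider (2 degrees of freedom for a two-model contrast, critical value 4.30 against 2.02), but that is the precision the design has.
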